### Objectives

The primary endpoints are major respiratory complications within 30 days after surgery. These respiratory complications involve respiratory distress or failure after the operation with continuation of mechanical ventilation, pulmonary atelectasis requiring sputum suction by bronchoscopy, pneumonia requiring specific antibiotics confirmed by thoracic X-ray or CT scan of the thorax and a positive sputum culture, and acute respiratory distress syndrome.

The secondary endpoints include other postoperative complications not involved in the primary endpoints according to systematic classification of morbidity and mortality after thoracic surgery.^25^ Other secondary endpoints include change of pulmonary function preoperatively and 3 months postoperatively, intraoperative variables involving volume of blood loss, duration of operation, the number and location of lymph nodes dissected, postoperative pain scale evaluated by pain score and quality of life questionnaires (EORTC QLQ-C30 and QLQ-0ES18), in-hospital mortality and 30-day mortality rate, the length of hospital stay, total expenses in hospital, 2 year survival rate, and survival at 5 years. The laboratory data include values for C-reactive protein and interleukin-6 from blood samples tested in the third and seventh day postoperatively in order to analyse the effect of MIO on surgery-related inflammatory reaction in the patients postoperatively.

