### Inclusion criteria

Subjects may enter the trial with all of the following: (1) oesophageal carcinoma confirmed by pathology; (2) resectable thoracic oesophageal carcinoma in cT1b-4aN0-2M0 using chest CT preoperatively, ultrasonography of the abdomen, head CT and bone scan; (3) oesophageal carcinoma that can be resected initially by multidisciplinary treatment, or that can be resected after neoadjuvant therapy; (4) age between 18 and 75 years; (5) Eastern Cooperative Oncology Group Performance Status (ECOG PS) score ≤2; (6) a life expectancy ≥12 months; (7) tolerate tracheal intubation and general anaesthesia as determined by an anaesthetist preoperatively; (8) laboratory findings including liver and kidney function, and electrolyte findings in 14 days before operation meet the criteria; (9) informed consents must be signed before the beginning of any procedures in the study.

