### Sample size calculation

According to the literature, the incidence of respiratory complications after oesophagectomy for oesophageal carcinoma is 27–31%.^2^
^3^ Therefore, we plan to decrease the incidence rate of respiratory complications from 30% to 20% with minimally invasive thoraco-laparoscopic oesophagectomy. This is based on a unilateral significance level of α=0.025 and a power of β=0.8. After adding 10% loss of the sample, 324 patients will be required for each group so a total of 648 patients will finally be enrolled into the study.

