### Statistical analysis

Statistical analyses are carried out using SPSS software for Windows, V.16.0 (SPSS Inc, Chicago, Illinois, USA). Continuous variables are presented as mean±SD and compared using Student's t test or analysis of variance (ANOVA) test. Categorical variables will be reported as absolute numbers (frequency percentages) and analysed using χ^2^ test. Survival will be estimated by means of Kaplan-Meier curves, and survival compared using log-rank test. A two-tailed p<0.05 is considered statistically significant.

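### The only test stated for the binary primary endpoint is an unadjusted χ² test; it is valid and matches the sample size, but leaves unused baseline predictors that the trial already records

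*Protocol article*

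**What the plan says.** - **Endpoint** (Objectives): "The primary endpoints are major respiratory complications within 30 days after surgery". A patient either has such an event or does not, so the endpoint is binary.
- **Test** (Statistical analysis): "Categorical variables will be reported as absolute numbers (frequency percentages) and analysed using" a χ² test. The section does not name the primary endpoint, and it mentions no adjusted or stratified analysis. Its significance rule is "A two-tailed p<0.05 is considered statistically significant".
- **Sample size** (Sample size calculation): the target is put as "we plan to decrease the incidence rate of respiratory complications from 30% to 20% with minimally invasive thoraco-laparoscopic oesophagectomy". The design takes a one-sided α of 0.025 and 80% power, allows for 10% loss, and arrives at 324 per arm, 648 in all.
- **Baseline data already collected**: the secondary endpoints in Objectives include "change of pulmonary function preoperatively and 3 months postoperatively", so a preoperative lung-function value is needed. The Inclusion criteria list "4) age between 18 and 75 years; (5) Eastern Cooperative Oncology Group Performance Status (ECOG PS) score ≤2", so age and performance status must be known for every patient who enters.

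**The concern.** The primary endpoint combines respiratory failure, atelectasis, pneumonia and acute respiratory distress syndrome. Lung function before surgery, age and performance status are natural candidate predictors of such events. The plan uses lung function to describe a secondary outcome but not to sharpen the respiratory comparison for which the trial is sized.

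An unadjusted test leaves any outcome variation that these covariates explain in the error term. The trial is planned at 80% power with no margin after the allowed 10% loss, so any precision recovered would serve its main question. The covariates also have to be chosen before outcomes are seen. An adjusted analysis chosen afterwards would carry little weight.

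**Working it through.** **Inputs.** From the Sample size calculation section: 30% (open) and 20% (minimally invasive), one-sided α = 0.025, power 0.80, 10% loss, 324 per group. One-sided 0.025 and two-sided 0.05 share the critical value 1.96, so the two sections agree. The share of outcome variance explained by the covariates, R², is not in the document and is assumed to lie between 0 and 0.15.

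**Step 1: reproduce 324.**
- Unpooled variance: n = (0.30×0.70 + 0.20×0.80) × (1.960 + 0.842)² / 0.10² = 0.37 × 7.849 / 0.01 = 290.4, so 291 per arm. Then 291/0.9 = 323.3, so **324**.
- Pooled variance: n = (1.960×√0.375 + 0.842×√0.37)² / 0.10² = 293.2, so 294 per arm. Then 294×1.10 = 323.4, so **324** (or 294/0.9, so 327).
- With a continuity correction, n is 313 per arm, then 345 to 348. That does not reproduce 324.

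The stated size is therefore that of an unadjusted comparison of two proportions. This supports reading the χ² rule as the primary test.

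**Step 2: power of the planned test.** Evaluable per arm: 324×0.9 = 291.6, about 292. Power = Φ[(0.10√n − 1.960√0.375)/√0.37]. At n = 292 this is Φ[(1.709 − 1.200)/0.608] = Φ(0.836) = **79.8%**. The planned 80% is delivered.

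**Step 3: power with adjustment, by approximation.** Replace n by the effective size n/(1 − R²). The last column is the enrolment per arm that would give 80% power: 294×(1 − R²), rounded up, divided by 0.9, rounded up.

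| Assumed R² | Effective n per arm | Power | Gain (points) | Enrolment for 80% |
|---|---|---|---|---|
| 0 | 292 | 79.8% | 0 | 327 |
| 0.02 | 298 | 80.6% | 0.8 | 322 |
| 0.05 | 307 | 81.8% | 2.0 | 312 |
| 0.10 | 324 | 83.8% | 4.0 | 295 |
| 0.15 | 344 | 85.9% | 6.0 | 278 |

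For scale, R² = 0.10 is worth about as much as losing no patients at all: 324 evaluable per arm also gives 83.8%.

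**Step 4: check by simulation.** One normally distributed, fully observed risk score; marginal rates held at 30% and 20%; 292 per arm; 4,000 trials per setting; test of the arm coefficient in a logistic model.

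| Control-arm R² | AUC | Unadjusted | Adjusted |
|---|---|---|---|
| 0 | 0.50 | 80.4% | 80.4% |
| 0.02 | 0.58 | 79.4% | 80.2% |
| 0.05 | 0.64 | 80.4% | 81.9% |
| 0.09 | 0.68 | 80.0% | 83.1% |
| 0.16 | 0.74 | 79.2% | 85.3% |

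The Monte Carlo standard error of each power figure is about √(0.8×0.2/4000) = 0.6 points. A separate simulation of the standardised risk difference itself, with 291 per arm, gave 79% to 80% at AUC 0.61, 80% to 82% at 0.65, 80% to 84% at 0.69 and 80% to 85% at 0.73. Under the null, rejection rates were 4.2% to 5.5% for both methods.

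**Step 5: a more realistic case.** With three covariates, 5% of lung-function values mean-imputed and 291 per arm, power went from 79.0% to 79.3% when the covariates carried no information. It rose by about 1 to 3 points under modest to stronger prognosis. Type I error was 5.0% to 6.1%.

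**The case against.** The strongest case against is that nothing here is wrong. The χ² test is valid, it matches the sample size, and the planned 80% is met. This stands. A reader might infer that the trial is underpowered or is giving away planned power; Steps 1 and 2 show that it is not. A reader might also infer that chance imbalance in baseline lung function biases the crude test. It does not: randomisation covers this, and the crude test held its error rate in simulation.

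Second, covariate lists and model form are usually left to the statistical analysis plan, which is not shown. That would dispose of a complaint about silence. Here the article states a method, and the method is unadjusted. If the analysis plan already specifies adjustment, only the article's wording needs to be aligned with it. It is also true that the Statistical analysis section reaches the primary endpoint only by implication.

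Third, the size of the benefit is assumed. This stands too. The document does not say how well these covariates predict respiratory events. Nor can a wide spread of risk be inferred from the entry limits: age is capped at 75, ECOG above 2 is excluded, and the Exclusion criteria remove severe comorbidity. The larger simulated gains also rest on a single, perfectly measured risk score.

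Fourth, adjustment is not free. The lung-function measure is not named, its timing relative to randomisation is not stated, and it is not an entry criterion, so the amount of missing data is unknown. A logistic model reports a conditional odds ratio unless its results are standardised. These are practical matters that can be settled in advance. They rule out calling the gain cost-free, but they do not remove it.

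**Conclusion.** The point holds as a missed efficiency, not as an error or a shortfall against the plan. The published text commits binary outcomes, and so by implication the primary endpoint, to an unadjusted test while candidate predictors are already on record.

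The gain from adjustment runs from essentially zero, if the covariates are weak, to about 1 to 6 power points over an assumed R² of 0.02 to 0.15. Up to an R² of about 0.05 it is 2 points or fewer. With three covariates and some imputation, 1 to 3 points is the more realistic expectation. Uninformative covariates cost no power in the case simulated. The change is worth making because it keeps the planned contrast and is inexpensive, not because the present test fails.

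**What to change.** Amend the Statistical analysis section, and the analysis plan if needed, before outcomes are examined:

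- **Primary analysis**: a logistic model for any major respiratory complication within 30 days, with arm, one named preoperative lung-function measure (continuous), age (continuous) and ECOG performance status.
- **Reported effect**: the standardised (marginal) risk difference with a robust 95% confidence interval and p-value. This keeps the estimand that the sample size assumes, 30% versus 20%.
- **Baseline data**: state which lung-function value is used and that it predates randomisation. Impute missing baseline values simply, without reference to arm or outcome.
- **Supporting analysis**: the crude χ² test.
- **Variance check**: one simulated type I error reached 6.1%, so confirm the robust standard error at this sample size before the plan is locked.

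The sample size need not change; the gain serves as margin. The cost is a few sentences, the choice of covariates in advance, the imputation rule, and extra programming that may have to be done outside SPSS 16.0. No new patients are required and, where lung function is measured as planned, no new data.

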## Methods and analysis

This is a 3 year multicentre, prospective, randomised, open and parallel controlled trial, which aims to compare the effectiveness of minimally invasive thoraco-laparoscopic oesophagectomy to open three-stage transthoracic oesophagectomy for resectable oesophageal cancer.

Patients with resectable thoracic oesophageal carcinoma in cT1b-4aN0-2M0 are eligible for inclusion using chest CT, ultrasonography of the abdomen, head CT, and bone scan.^24^ We do not include a positron emission tomography (PET)/CT scan as a preoperative workup because medical insurance does not cover the expense of PET/CT. Cervical oesophageal cancer and adenocarcinoma of the oesophagogastric junction are excluded. In China, cervical oesophageal cancer is treated mainly with radiotherapy, and cancer of the oesophagogastric junction is resected via a single left thoracic approach.

The patients are divided into two groups. Group A patients receive McKeown MIO which involves thoracoscopic oesophagectomy and laparoscopic gastric mobilisation with cervical anastomosis. Group B patients receive open McKeown oesophagectomy, which involves a right thoracotomy and laparotomy with cervical anastomosis. All patients received two field lymphadenectomy which involves resection of the lymph nodes in the thorax and abdomen. The flow chart for the trial is shown in figure 1. Neo-adjuvant chemotherapy will be performed for patients according to local guidelines of the participating cancer hospital.

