### Randomisation

When the eligible patients are confirmed and informed consent is obtained, the researchers login through the trial randomisation system and input the patient's number and other related information. Then the patient is randomised to either the open three-stage transthoracic oesophagectomy group or the minimally invasive thoraco-laparoscopic oesophagectomy group through a group number produced by SPSS software.

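### The log-rank test for survival, a secondary endpoint, names no strata, although clinical stage is an entry criterion; stratifying by broad stage group could add some power at very little cost

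*Protocol article*

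**What the plan says.** The protocol article (Statistical analysis) gives one method per type of data. For survival it reads: "Survival will be estimated by means of Kaplan-Meier curves, and survival compared using log-rank test". No stratum or covariate is named. The significance rule is "A two-tailed p<0.05 is considered statistically significant".

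Inclusion criterion 2 requires "resectable thoracic oesophageal carcinoma in cT1b-4aN0-2M0 using chest CT preoperatively, ultrasonography of the abdomen, head CT and bone scan". A T and an N category must therefore be assigned before a patient can be called eligible. Methods and analysis adds: "We do not include a positron emission tomography (PET)/CT scan as a preoperative workup".

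Under Randomisation, eligible and consenting patients are allocated "through a group number produced by SPSS software". No stratification is stated.

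Under Objectives, survival appears among the secondary endpoints as "2 year survival rate, and survival at 5 years". The primary endpoint is different: "The primary endpoints are major respiratory complications within 30 days after surgery". The sample size rests on that endpoint alone.

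**The concern.** The admitted stages run from submucosal, node-negative tumours to cT4a N2 disease. If mortality differs widely over that range, a single pooled log-rank test compares arms within risk sets of mixed prognosis. High-stage patients die first. Where treatment has an effect, the stage mix of those still at risk then drifts apart between the arms, and the overall hazard ratio moves closer to 1 than the hazard ratio within a stage. Chance differences in stage between the arms also add noise. As the article is written, stage is controlled neither at allocation nor in the analysis.

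This matters because the Discussion hypothesises fewer respiratory complications without loss of oncological clearance, and survival bears on the second half of that. A less sensitive test makes a non-significant survival result more likely, and such a result could be read as reassurance. The trial was not sized for survival, so power there is not in surplus.

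**Working it through.** **The plan's own figure.** The inputs are 30% v 20%, one-sided α = 0.025, power 80% and 10% loss (Sample size calculation). With pooled variance, n = [1.96·√(2·0.25·0.75) + 0.842·√(0.30·0.70 + 0.20·0.80)]² / 0.10² = 293.2, so 294 per arm. Then 294 × 1.1 = 323.4, so 324 per arm and 648 in total. The stated size reproduces. It involves no survival input, so this point does not touch it.

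**Inputs for survival.** From the article: 648 patients, 1:1, 10% loss, two-sided 5% test. The article gives no survival rate, hazard ratio (HR), number of deaths or prognostic strength of stage. These were assumed:
- control survival 65% at 2 years or 40% at 5 years, exponential within stage;
- four stage groups holding 25%, 35%, 25% and 15% of patients;
- stage hazards equal, moderate (1:1.5:2:3) or strong (1:2:4:6);
- within-stage treatment HR 0.70, 0.75 or 0.80;
- allocation without regard to stage.

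**Statistic.** At each death, the observed treatment indicator minus its expected value p (the share of the risk set in that arm) is summed to U, and p(1−p) is summed to V; Z = U/√V. The stratified test forms U and V within each stage group and adds them before dividing. Each case used 4,000 runs. The standard error of a power estimate is at most √(0.25/4000) = 0.8 points. Both tests were applied to the same data sets.

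**Power in %, unstratified → stratified** (differences in points, taken before rounding):

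| Follow-up | Stage hazards | HR 0.70 | HR 0.75 | HR 0.80 |
|---|---|---|---|---|
| 2 years | equal | 68.5 → 68.2 (−0.3) | 51.5 → 51.3 (−0.2) | 34.5 → 34.3 (−0.2) |
| 2 years | moderate | 66.1 → 67.9 (+1.8) | 48.9 → 50.8 (+1.9) | 32.9 → 34.2 (+1.4) |
| 2 years | strong | 62.7 → 68.7 (+6.0) | 47.1 → 52.0 (+4.9) | 31.1 → 34.7 (+3.5) |
| 5 years | equal | 90.1 → 90.0 (−0.1) | 75.9 → 75.1 (−0.8) | 53.9 → 53.7 (−0.2) |
| 5 years | moderate | 87.3 → 89.9 (+2.6) | 72.4 → 75.4 (+3.0) | 51.2 → 54.9 (+3.7) |
| 5 years | strong | 82.2 → 90.3 (+8.2) | 65.0 → 77.1 (+12.1) | 43.8 → 53.6 (+9.8) |

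**Finer strata.** With all 12 cT × N cells (3,000 runs, HR 0.75) the change was −0.5 to +3.3 points at 2 years and −0.7 to +9.4 at 5 years, so splitting finely brings no advantage.

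**A weaker gradient.** With three equal groups, hazards 1:1.5:2, an assumed mean control hazard of 0.25 per year, 10% loss and HR 0.75, power went from 53.9% to 54.6% at 2 years (+0.7) and from 80.1% to 81.9% at 5 years (+1.8).

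**Type I error.** At HR 1.0, both tests rejected in 4.5% to 5.5% of runs across the four-group and 12-cell cases.

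**Limits.** By Schoenfeld's formula, deaths needed for 80% power are 4(1.96 + 0.842)²/(ln HR)²: 247 at HR 0.70, 380 at 0.75 and 631 at 0.80. The four-group runs gave about 188 to 200 deaths at 2 years and 333 to 352 at 5 years over HR 0.70 to 0.80. Stratifying recovers efficiency; it does not make survival an adequately powered endpoint at HR 0.75 or weaker.

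**The case against.** The strongest objection is that nothing here is wrong. The article says only that a log-rank test will be used. It does not say unstratified, and an article commonly leaves the strata for a secondary endpoint to the full protocol or the analysis plan. A plain log-rank test also matches an allocation with no stated stratification, and its error rate already allows for chance imbalance. All of this stands. It makes the point an optional improvement.

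A reader might infer that the planned test is biased towards no difference. The documents do not support that. They plan no hazard ratio, and an overall hazard ratio nearer 1 than the within-stage one is a different quantity, not a biased estimate of it.

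A reader might also expect a large gain. A steep gradient (1:3:6 in three equal groups, base hazard 0.11 per year, HR 0.75, no losses) takes 5-year power from 67.6% to 85.6%, which is 18 points. But the article gives no evidence of such a gradient and allows for 10% loss. Staging without PET/CT misclassifies some patients, and neoadjuvant treatment may blur the link between stage and survival. Nor does the Discussion posit a survival benefit as large as HR 0.70 to 0.75. With three equal groups, hazards 1:2:4 and HR 0.85, power rose only from 20.5% to 22.4% at 2 years and from 29.4% to 35.5% at 5 years.

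Finally, preoperative stage is ambiguous when neoadjuvant treatment is given, because the Randomisation section does not place allocation before or after it. That objection is right, and the replacement wording has to settle it.

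**Conclusion.** The point holds as a modest efficiency improvement for a secondary endpoint. The stated log-rank test is valid, but if stage is prognostic it gives up power that a stage-stratified test would keep. For a within-stage HR of 0.70 to 0.80, the gain runs from almost nothing to about 6 points at 2 years (about 5 at HR 0.75) and from about 2 to 12 points at 5 years. The loss is under 1 point if stage is not prognostic, and type I error is unchanged. Every survival input behind these figures is assumed, so the actual loss cannot be read from the documents.

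It would go too far to say that the trial certainly loses power, or that stratifying is entirely free. The cost is small but real, and an analysis plan that is not shown may already name the strata. The sample size and the primary comparison are unaffected.

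**What to change.** Replace the survival sentence, before any survival comparison by arm is seen, with:

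> Survival will be compared by a log-rank test stratified by clinical stage group as last recorded before randomisation (three groups: cT1b-2 N0; cT3-4a N0; any cT N1-2), with the hazard ratio and 95% CI from a Cox model stratified by the same groups. Kaplan-Meier curves will be shown by arm.

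Tying the stage to the last record before randomisation removes the ambiguity over neoadjuvant treatment and keeps the stratifier a true baseline value. Pathological stage should not be used: the number and location of nodes removed are themselves outcomes of the operation.

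The cost is one sentence, with no new patients, visits or data. The hazard ratio becomes conditional on stage and should be labelled so. Three broad groups avoid sparse cells but leave some variation inside them, notably in the node-positive group, so the gain may fall below the four-group figures; staging without PET/CT works the same way. If the full protocol or analysis plan already fixes strata, it is enough to confirm that.

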## Discussion

Although adenocarcinoma of the oesophagus has become the main type of oesophageal cancer in western countries, oesophageal SCC is still the predominant histologic type in China. Therefore, both Ivor-Lewis and McKeown oesophagectomy are important in the surgical treatment of oesophageal SCC. The TIME and MIRO trials concluded that MIO is not only feasible, but perhaps superior to open oesophagectomy. However, there are no RCTs designed to compare the outcome of the MIO McKeown procedure and the open McKeown procedure for oesophageal SCC, apart from one study which aims to compare the outcomes of McKeown MIO with or without neo-adjuvant chemoradiotherapy (NCT02188615) for squamous cell oesophageal cancer. Therefore, we are conducting this study, which aims to investigate the difference between the MIO McKeown procedure and the open McKeown procedure for oesophageal SCC.

Maas *et al*^8^ found that less surgical trauma could lead to better preserved acute-phase and stress responses and fewer clinical manifestations of respiratory infections in patients who underwent MIO compared to those who underwent open oesophagectomy. Our previous study showed that the overall morbidity rate was significantly decreased in the MIO McKeown group compared with the open McKeown group, and no significant differences were found in the number of harvested lymph nodes.^13^ For these reasons, we hypothesise that the MIO McKeown procedure may result in a significant decrease in major respiratory complications compared with the open McKeown procedure for oesophageal SCC, without comprising the oncologic clearance.

This is the largest multicentre, prospective, RCT designed to compare open McKeown oesophagectomy with MIO McKeown oesophagectomy for oesophageal cancer in China. We hope the results of this study will add new evidence to support the use of MIO in the surgical treatment of oesophageal cancer.
